**PROTOCOL OVERVIEW AND INTRODUCTION:**

In the United States, cardiovascular disease causes over one-third of all deaths and vitamin D deficiency is epidemic. An increasing body of data suggests that low vitamin D status adversely impacts the cardiovascular system. It is our fundamental hypothesis that vitamin D deficiency is a risk factor for cardiovascular disease by causing a cytokine mediated pro-inflammatory milieu leading to endothelial dysfunction. Moreover, we hypothesize that vitamin D supplementation will reduce inflammation, thus restoring endothelial function and thereby reducing cardiovascular disease risk. To begin testing these hypotheses, the specific aims of this pilot study are to investigate the effect of vitamin D baseline status (as defined by serum 25-hydroxyvitamin D [25(OH)D] measurement) and subsequent vitamin D therapy on endothelial function, arterial stiffness, and selected plasma biomarkers of inflammation.

This pilot research will be conducted in 80 post-menopausal women where 40 will receive vitamin D3 2,500 IU daily, the others matching placebo. This study will explore the effects of vitamin D on plasma markers of inflammation, endothelial function, and arterial stiffness. Postmenopausal women aged 55-65 years are chosen due to their highest risk for development of a subsequent new cardiovascular disease diagnosis. All study participants will have fasting laboratory and noninvasive vascular ultrasound studies performed at baseline and four months later. The primary outcome measure of this pilot study is change in markers of endothelial function and arterial stiffness with vitamin D3 therapy. Changes in plasma biomarkers of inflammation with vitamin D3 therapy are secondary outcome measures. If these hypotheses are correct, our long-term goals include investigation of the effect of vitamin D repletion on subclinical atherosclerosis and subsequent cardiovascular events.

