**D. Endothelial Dysfunction, Cardiovascular Disease and Vitamin D Status**

Measurement of endothelial function has recently emerged as a useful CVD research tool and serves as a “barometer” for CV health.(31) For example, severity of endothelial dysfunction relates to the risk for initial or recurrent CV event.(32-35) Additionally, a number of interventions that reduce CV risk also improve endothelial function.(36-41) This could be anticipated in that the endothelium acts to maintain vascular homeostasis through multiple complex interactions with cells in the vessel wall and lumen.(42) The endothelium regulates vascular tone by balancing production of vasodilators and vasoconstrictors. It modulates blood fluidity and coagulation through production of factors that regulate platelet activity, as well as the clotting cascade and fibrinolytic system. Finally, the endothelium has the capacity to produce cytokines and adhesion molecules that regulate and direct the inflammatory process.(43) In healthy individuals, the endothelium responds to these stimuli by releasing vasodilatory factors, particularly nitric oxide [NO]. People with angiographically proven CAD display impaired flow-mediated dilation [FMD] reflecting loss of NO and unopposed constrictor effects.(44) Measures of arterial stiffness that are affected by endothelial function, including pulse wave velocity, central aortic blood pressure and augmentation index, predict CV events.(45, 46) As such, the endpoints chosen for this research (FMD, pulse wave velocity, central aortic pressure, and aortic augmentation index) are accepted surrogates of endothelial function and arterial stiffness.

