**HYPOTHESES AND SPECIFIC AIMS**

Our fundamental hypothesis is that low vitamin D status is a risk factor for CVD by causing a proinflammatory milieu, thereby leading to endothelial dysfunction. Additionally, we hypothesize that vitamin D supplementation will reduce inflammation, thereby restoring endothelial function and ultimately reducing CVD risk. To begin testing these hypotheses, the specific aims of this pilot study are to investigate:

1. The effect of vitamin D status, as defined by serum 25-hydroxyvitamin D [25(OH)D], on endothelial function, arterial stiffness, and selected plasma biomarkers of inflammation.
2. The effect of subsequent vitamin D therapy on endothelial function, arterial stiffness, and selected plasma biomarkers of inflammation.

To this end, we hypothesize that low vitamin D status is associated with increased circulating levels of inflammatory biomarkers. Though the primary outcome measure of this pilot study is change in markers of endothelial function and arterial stiffness with vitamin D3 therapy, changes in circulating inflammatory biomarkers are being proposed here as secondary outcome variables. If these hypotheses are correct, our long-term goals include investigation of the effect of vitamin D repletion on subclinical atherosclerosis and subsequent cardiovascular events. Ultimately, these future studies will be necessary to determine whether vitamin D supplementation could reduce future CVD events and mortality.

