**ANALYTICAL APPROACHES AND CONSIDERATIONS**

1. **Power Calculation**

In experienced laboratories with excellent reproducibility (such as in [name] CV research lab), a 2% to 3% improvement in FMD can be detected in parallel-groups trials with about 25 to 45 subjects per treatment arm.(97-99) Power calculation shows that 37 subjects in each arm of this parallel group study should enable us to detect a 3% change in FMD with 80% power using a two-sample t-test with two-sided 5% level if the standard deviation of %FMD is similar to that observed by Sorenson.(98) Allowing for an 8% drop out rate, we plan to recruit 40 subjects per arm.

Endothelial function will be evaluated by measuring brachial artery FMD using ultrasound. Studies will be read in subject pairs (baseline and four months), blinded to study time point and treatment. Output data will include heart rate, brachial artery blood pressure, brachial artery diameter, reactive hyperemia VTI, and FMD at each time point.

Arterial stiffness will be determined from arterial tonometry using an AtCor Sphygmacor Px arterial tonometry system. Studies also will be read as described above. Output data will include heart rate, derived pulse wave velocity, central aortic systolic and diastolic pressure and aortic augmentation index, read independently and standardized to a heart rate of 75 bpm. The proposed sample size (37 per group or 74 total) will be sufficient to detect an ~10% reduction in pulse wave velocity with a standard deviation of approximately 15%, with at least 80% power using a two-sample, two-sided t-test with 5% level of significance. Thus, allowing for an 8% drop out rate, we plan to recruit 40 subjects per arm. Extrapolating from population-based studies,(100, 101) a 10% change in pulse wave velocity would predict a significant reduction in CVD risk.

1. **Statistical Analysis**

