The primary endpoint is change in endothelial function from baseline after 16 weeks of vitamin D supplementation compared to placebo. The primary comparison will be made using a two-tailed Student's t-test. Multivariable linear regression modeling will be used to evaluate predictors of changes in FMD, including 25(OH)D levels, age, sex, and other CV risk factors. For the cross-sectional baseline analysis, Pearson correlations will be used to determine associations with FMD, and multivariable linear regression modeling will be used to determine independent baseline associations. Similar analyses will be performed for pulse wave velocity, central aortic pressure and aortic augmentation index.

Similar analyses will be performed for changes in plasma biomarker levels (hs-CRP, IL-6, TNF-, sICAM and sVCAM) from baseline to the 16-week follow-up. The proposed sample size of 37 subjects per group will permit us to detect differences between groups of 0.6-0.7 pg/ml in IL-6, 0.4-0.5 pg/ml in TNF- and 39-53 ng/ml in sICAM levels using a two-sample t-test with Type 1 error rate of 5% and 80% power if the standard deviations of cytokine levels are similar to those observed by Marketou.(102) As stated above, we plan to recruit 40 subjects per arm allowing for an 8% drop out rate.

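### The protocol defines the primary outcome in two ways and gives no rule linking them, so it does not secure the 5% level and 80% power for the primary claim

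*Protocol*

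**What the plan says.** Two sections of the protocol describe a primary outcome that spans two constructs. The Protocol Overview and Introduction says "The primary outcome measure of this pilot study is change in markers of endothelial function and arterial stiffness with vitamin D3 therapy". Hypotheses and Specific Aims says the same: "the primary outcome measure of this pilot study is change in markers of endothelial function and arterial stiffness with vitamin D3 therapy". Both sections then class the inflammatory biomarkers as secondary.

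The Statistical Analysis section, under Analytical Approaches and Considerations, names one construct: "The primary endpoint is change in endothelial function from baseline after 16 weeks of vitamin D supplementation compared to placebo". It attaches one test: "The primary comparison will be made using a two-tailed Student's t-test". For stiffness it adds "Similar analyses will be performed for pulse wave velocity, central aortic pressure and aortic augmentation index" and gives those measures no rank.

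Two other places bear on the reading. Background section D, speaking of both constructs together, says "the endpoints chosen for this research (FMD, pulse wave velocity, central aortic pressure, and aortic augmentation index) are accepted surrogates"; this lists four measures without ranking them. The Power Calculation section sizes the trial for FMD at a two-sided 5% level, and then for PWV "with at least 80% power using a two-sample, two-sided t-test with 5% level of significance", arriving at the same 37 evaluable and 40 recruited per arm.

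**The concern.** Which endpoint is primary is something the protocol itself should fix, and a reader can defend either definition from this text. The Overview and the Aims draw an explicit line with stiffness on the primary side. The Statistical Analysis section leaves stiffness out of the primary endpoint but never calls it secondary.

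The choice matters because the stated 5% level and 80% power hold together only if FMD is the sole primary endpoint. If stiffness is also primary, the error rate or the power changes, depending on a success rule that the protocol does not give. An investigator facing a null FMD result and a favourable PWV result could point to the Overview and call the trial positive; in the reverse case, the Statistical Analysis section would serve.

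**Working it through.** **Inputs.** From the Power Calculation section: 37 evaluable per arm; two-sided 5%; 80% power; FMD difference 3%; PWV difference 10% with SD 15%. From Background section D: four vascular measures. The FMD standard deviation is not given as a number, only by reference to a cited study. No correlations between measures are given, so those below are assumptions.

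**1. Reproduce the plan's own figure (PWV).**
n per arm = 2 × (1.960 + 0.842)² × (15/10)² = 2 × 7.85 × 2.25 = 35.3, rounded up to 36 (normal approximation). With the t distribution it is 36.3, rounded up to 37. Power at 37 per arm is 81.8% (normal) or 80.8% (t). The stated 37 and the stated power of at least 80% both reproduce.

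For FMD, 37 per arm and 80% power imply a standardised difference of 0.660, that is an SD of 3/0.660 = 4.54 (4.61 by the normal approximation). This is solved back from the stated result and is no independent check.

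**2. FMD alone is primary.** One test at two-sided 5%: type I error 5%, planned power 80%.

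**3. Success on any one marker counts.** For k independent tests the chance of at least one false positive is 1 − 0.95^k:
- k = 2 (FMD, PWV): 1 − 0.9025 = 9.75%
- k = 4 (FMD, PWV, central aortic pressure, augmentation index): 1 − 0.8145 = 18.5%

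With equally correlated test statistics (simulation, one million draws):

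| Assumed correlation | 2 measures | 4 measures |
|---|---|---|
| 0 (exact) | 9.75% | 18.5% |
| 0.3 | 9.5% | 17.4% |
| 0.5 | 9.1% | 15.6% |
| 0.8 | 7.8% | 11.4% |

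**4. FMD and PWV must both succeed.** No alpha split is needed. Joint power at 37 per arm, if independent, is 0.80 × 0.808 = 0.646, about 65%. Positive correlation would raise this, but never above 80%, the lower of the two separate powers.

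**5. Stiffness stays primary under either-suffices, with Bonferroni control.**
- FMD and PWV at 0.025 each: power at 37 per arm falls to 70.8% for FMD and 71.8% for PWV (t). Restoring 80% needs 45 evaluable per arm, and 45/0.92 = 48.9, so 49 recruited.
- All four measures at 0.0125 each: power at 37 per arm is about 61% for FMD and 62% for PWV. Restoring 80% needs 53 evaluable per arm for FMD, and 53/0.92 = 57.6, so 58 recruited.

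The FMD figures in this step rest on the back-solved 0.660. The PWV figures use the stated 10/15 = 0.667.

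**The case against.** The best defence is that the Statistical Analysis section is the operative one. It names one endpoint and one test, and the Power Calculation section makes clear that endothelial function is measured by brachial FMD. Read alone, it controls the primary test at 5%. That stands. A reader might infer that the trial has no 5% error control at all, and the document does not support this: control is present under one of its two definitions and unsettled under the other.

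Three further inferences also go too far.
- **That powering PWV at 5% makes it primary.** The Statistical Analysis section also gives detectable differences for IL-6, TNF and sICAM at a 5% type I error, and those biomarkers are expressly secondary. Only the wording of the Overview and the Aims makes stiffness primary.
- **That any one of the markers suffices.** No success rule is stated anywhere. The Overview and the Aims could equally mean that both constructs must succeed, in which case the cost is power and not alpha. The four-measure list comes from a background sentence that does not call the measures primary. Counting central systolic and diastolic pressure as separate endpoints, for a total of five, has still less support, since Background section D and the Statistical Analysis section treat central aortic pressure as one endpoint.
- **That the independence figures are the expected ones.** The stiffness measures come from the same tonometry system, so independence is the least plausible case for them.

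The study also calls itself a pilot, and alpha allocation may sit in an analysis plan that is not at hand. Both points lower the stakes. Neither removes the contradiction: an analysis plan that adopted either definition would still conflict with part of this protocol.

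**Conclusion.** The inconsistency is real and appears on the face of the protocol: stiffness belongs to the primary outcome in the Overview and the Aims, but not in the Statistical Analysis section. With no either/both rule, alpha split or testing order, the document does not secure the stated 5% and 80% for the primary claim.

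The size depends on the reading. It is nil if FMD alone is primary. If any marker suffices, the false-positive chance is about 7.8–9.8% for two measures or 11–19% for four, over assumed correlations from 0.8 to 0. If FMD and PWV are both required, alpha holds and joint power is about 65% under independence. The sample-size arithmetic for PWV is sound, and this point does not question it.

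**What to change.** Amend the Protocol Overview and Introduction and Hypotheses and Specific Aims to match the Statistical Analysis section. The single primary endpoint would be change in brachial FMD from baseline to the end-of-treatment visit, compared between arms at two-sided 5%. Use one label for that visit throughout, since the protocol calls it 16 weeks in one place and four months in others.

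List PWV, central aortic pressure and augmentation index as secondary outcomes alongside the biomarkers, reported as estimates with 95% confidence intervals. In the Power Calculation section, say that the PWV statement applies to a secondary outcome. Make the change before unblinding, so that the choice cannot look driven by the data.

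The cost is small. The sample size stays at 37 evaluable per arm with no added procedures, and the sponsor gives up calling a stiffness result primary. If stiffness is to remain primary, the protocol should state whether either or both must succeed, give the alpha allocation, and redo the sample size; for FMD and PWV under Bonferroni that means about 49 recruited per arm.

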**BACKGROUND**

**A. Cardiovascular Disease**

Cardiovascular disease (CVD) is the leading cause of mortality worldwide and causes over 36% of deaths annually in the United States. There is general agreement that age, family history, smoking status, dyslipidemia, hypertension and diabetes mellitus are causally linked risk factors for CVD. However, currently unappreciated CV risk factors may well exist; one such factor could be vitamin D inadequacy.(1)

**B. Vitamin D**

The vitamin D status of an individual is best evaluated by measurement of circulating 25(OH)D concentration. The optimal circulating 25(OH)D level has been suggested to be ~30 ng/ml or above, a value associated with maximal parathyroid hormone suppression and reduced fracture rate.(2) Using this definition, it has been estimated that approximately half of all adults in the United States have inadequate vitamin D status.(3) Therefore, if low vitamin D status contributes to the development of CVD, it is plausible that a large portion of the population may potentially be targeted for risk modification/reduction by optimization of their vitamin D status.

Vitamin D is produced in the skin when 7-dehydrocholesterol is converted to vitamin D3 (cholecalciferol) by ultraviolet B radiation.(4) Additionally, dietary or supplement intake of vitamin D contributes to circulating levels of vitamin D2 (ergocalciferol) and D3. Subsequently, vitamin D is activated by hydroxylation at 25 and 1 carbons in the liver and kidney respectively to form the active form, 1,25-dihydroxyvitamin D (calcitriol).(5) Calcitriol is important in intestinal calcium transport; thus, vitamin D deficiency has classically been recognized to cause decreased calcium absorption and impaired bone mineralization. However, it is increasingly being recognized that both 25-hydroxyvitamin D and 1,25-dihydroxyvitamin D are important in optimal function of multiple tissues and organ systems.(6) The CV system may be one such system.

**C. Vitamin D and the Cardiovascular System**

Although it has been classically accepted that 1--hydroxylation of 25-hydroxyvitamin D [25(OH)D] to the active form, 1,25-dihydroxvitamin D [1-25(OH)2D] occurs in the kidney, it is now appreciated that 1-25(OH)2D is also produced by local 1-hydroxylases in various extra-renal tissues. Extra-renal 1-25(OH)2D production is dependent on circulating levels of 25(OH)D. As locally produced 1-25(OH)2D plays an important autocrine role,(6) vitamin D deficiency could be expected to have adverse local consequences. For example, in the CV system, as vitamin D receptors are present in endothelium,(7) vascular smooth muscle(8, 9) and cardiomyocytes,(10) it is possible that low vitamin D status could adversely affect both cardiac and vascular function. Moreover, circulating 1-25(OH)2D3 is an important regulator of systemic calcium metabolism and intracellular calcium homeostasis in various tissues.(6) Altered calcium dynamics due to vitamin D deficiency in smooth and/or cardiac myocytes could plausibly adversely affect CV function. Additional non-classical vitamin D actions include modulation of lymphocytic cytokine production,(11-13) regulation of growth and proliferation of vascular smooth muscle and cardiomyocytes,(14) stimulation of vascular tissue anticoagulant activity(15) and suppression of renin gene expression.(16-18). Based on the above, it is clear that vitamin D deficiency could plausibly contribute to increased CV risk.

In fact, CVD prevalence is related to availability of ultraviolet solar exposure in that epidemiologic data finds coronary artery disease (CAD) and hypertension rates to increase with distance from the equator. Specifically, greater CVD prevalence is observed in regions with less exposure to sunlight.(19-22) Cross-sectional studies have reported associations between lower vitamin D levels and plasma renin activity,(23) blood pressure(24, 25), coronary artery calcification(26, 27) and CVD (28, 29). A recent longitudinal prospective study involving offspring of the Framingham cohort supported earlier findings associating vitamin D deficiency with incident CVD.(30) In summary, biologically plausible mechanisms combined with epidemiological data suggest that vitamin D deficiency may be an unappreciated risk factor for the development of CVD. Despite this association of vitamin D deficiency and risk of CVD, the underlying mechanism(s) remain unknown. Altered endothelial function may be the key link for this association.

**D. Endothelial Dysfunction, Cardiovascular Disease and Vitamin D Status**

Measurement of endothelial function has recently emerged as a useful CVD research tool and serves as a “barometer” for CV health.(31) For example, severity of endothelial dysfunction relates to the risk for initial or recurrent CV event.(32-35) Additionally, a number of interventions that reduce CV risk also improve endothelial function.(36-41) This could be anticipated in that the endothelium acts to maintain vascular homeostasis through multiple complex interactions with cells in the vessel wall and lumen.(42) The endothelium regulates vascular tone by balancing production of vasodilators and vasoconstrictors. It modulates blood fluidity and coagulation through production of factors that regulate platelet activity, as well as the clotting cascade and fibrinolytic system. Finally, the endothelium has the capacity to produce cytokines and adhesion molecules that regulate and direct the inflammatory process.(43) In healthy individuals, the endothelium responds to these stimuli by releasing vasodilatory factors, particularly nitric oxide [NO]. People with angiographically proven CAD display impaired flow-mediated dilation [FMD] reflecting loss of NO and unopposed constrictor effects.(44) Measures of arterial stiffness that are affected by endothelial function, including pulse wave velocity, central aortic blood pressure and augmentation index, predict CV events.(45, 46) As such, the endpoints chosen for this research (FMD, pulse wave velocity, central aortic pressure, and aortic augmentation index) are accepted surrogates of endothelial function and arterial stiffness.

In a healthy condition, the endothelium maintains normal vascular tone and blood fluidity. There is little to no expression of pro-inflammatory cytokines. However, traditional and novel CVD risk factors initiate a chronic inflammatory process that is accompanied by a loss of vasodilator and anti-thrombotic factors and an increase in vasoconstrictor and pro-thrombotic products. In this regard, vitamin D also has intriguing immunoregulatory properties.(47, 48) For example, reduced levels of C-reactive protein (CRP), erythrocyte sedimentation rate and cytokines have been noted with higher 25(OH)D levels or after vitamin D supplementation in patients with multiple sclerosis(49, 50) and ankylosing spondylitis(51). Consistent with this, vitamin D may be of therapeutic benefit in several autoimmune disease and allograft rejection(52, 53) and may modulate disease severity by reducing inflammation. In two small trials, vitamin D supplementation lowered CRP levels.(54, 55) Reduction in inflammatory cytokines was also noted in patients with congestive heart failure when supplemented with vitamin D.(56, 57) This is intriguing given the well-documented association of CRP with CV risk as either a marker of inflammation or possibly even in a causal role.(58, 59) However, the possibility that vitamin D deficiency is causally related to CVD development via enhanced cytokine production remains unstudied.

Statins, agents accepted to reduce CV risk, may have anti-inflammatory and endothelial protective effects in addition to reducing lipids. It is plausible that some of these beneficial effects are related to vitamin D as a recent study found atorvastatin to raise serum 25(OH)D levels among patients with a recent acute coronary syndrome event.(60) It has been hypothesized that statins may even activate vitamin D receptors.(61) Vitamin D levels may have beneficial effects on the vascular system by reducing arterial stiffness. In a cohort of patients with end-stage renal disease, both serum 25(OH)D and 1-25(OH)2D were negatively correlated with aortic pulse wave velocity and positively correlated with brachial artery distensibility and FMD after adjustment for blood pressure and age.(62) Thus it is possible that the beneficial CV effects of statins are, in part, associated with vitamin D.

